## Methods

### Trial design

This is a prospective multi-centre controlled epidemiologic non-inferiority trial with an approximated population of 100,000 patients undergoing surgical procedures. A patient-focused and evidence-based PBM program has been implemented in four German University Hospitals. Different time slots for control, implementation and study phases according to a non-randomised stepped wedge trial design were allocated for control, implementation and intervention periods.

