### Participants

Four German university hospitals are participating in the study: Frankfurt, Bonn, Kiel, Muenster. The PBM program includes all patients undergoing surgical procedures ranging anywhere from: orthopaedic and visceral surgery, general surgery, cardiothoracic surgery, trauma, otorhinolaryngology, gynecology and obstetrics, urology, oral and maxillofacial surgery, vascular surgery, and neurosurgery to increase applicability of the evidence obtained during this trial. Exclusion criteria are: <18 years, ophthalmologic or dermatologic or outpatient surgery. If a patient has multiple hospital admissions during the study period, the first hospital stay will be analysed.

The control group will be composed of the patients treated according to the standard protocol in charge before implementation of the PBM program. A period of three months was allowed for the implementation of the PBM components. Patients treated after implementation will be allocated to the PBM cohort until July 2015.

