## Statistics

### Sample size and power calculation

According to preliminary data, the composite endpoint has an approximate incidence of 10%. A difference of 0,5% is set as the non-inferiority margin as this can be seen as the natural standard deviation. The level of significance of non-inferiority is determined be α = 2.5%. This is consistent with a two-sided 95% confidence range of 1 + α = 95% for the difference in the composite endpoint. A power of 1 + β = 80% is sought. As the number of patients treated in each of the four university hospitals vary, an exact sample size calculation is not possible to this date. However, we expect approximately 100,000 participating patients.

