### Statistical analysis

The primary aim is to prove non-inferiority of the intervention (PBM) cohort when compared with the control cohort stratified by center. The primary composite endpoint will be registered electronically by analysis of ICD-10 diagnoses and will be exported to a data base. It will be analysed with a one-sided Mantel-Haenszel test with significance level of α =2.5% for the odds ratio resulting in H0: OR ≥ OR* vs. H1 OR < OR* with OR* being derived from the incidence in the control cohort and an incidence rate of the PBM cohort which is increased by the non-inferiority margin of 0.5%. As secondary analysis, we will analyse two-sided 95% confidence interval for the difference in the frequency of the composite safety endpoint as well as for the odds ratios and the single components of the composite endpoint. Additionally, the influence of covariates, e.g. the calendar year, concomitant diseases, the asynchrony of the study periods at different sites will be assessed statistically. Should there be a significant influence on the incidence of the composite endpoint, the Mantel-Haenszel test will be supplemented with a respective multivariate approach accounting for covariates.

Secondary endpoints will be compared with a two-sided Wilcoxon-Mann–Whitney test using a significance level of α =5%. A subgroup analysis will assess if there is some bias from not excluding patients with multiple hospital stays for surgical intervention during the study period. A further subgroup analysis will assess if there is a difference of safety between a) elective patients who will receive preoperative haemoglobin optimisation compared to b) anemic patients who will not undergo preoperative haemoglobin optimisation due to failed postponement of surgery in case of surgical urgency or non-elective surgery, respectively.

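### The deciding non-inferiority test is a before-after comparison adjusted for centre only; case mix and calendar time enter only if significant and only as a supplement, so drift smaller than the margin can settle the verdict

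*Protocol article*

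**What the plan says.** All places are in the protocol article.

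- Trial design: control, implementation and intervention periods are allocated to the hospitals "according to a non-randomised stepped wedge trial design".
- Participants: controls are "patients treated according to the standard protocol in charge before implementation of the PBM program". Three months are allowed for implementation, and patients treated after it form the PBM cohort.
- Sample size and power calculation: "A difference of 0,5% is set as the non-inferiority margin", on a composite rate of about 10%.
- Statistical analysis: the aim is non-inferiority of the PBM cohort "when compared with the control cohort stratified by center", by a "one-sided Mantel-Haenszel test with significance level of α =2.5% for the odds ratio".
- The same section lists calendar year, concomitant diseases and the differing site periods as examples of covariates whose influence will be assessed. It then sets the rule for acting on that assessment: "Should there be a significant influence on the incidence of the composite endpoint, the Mantel-Haenszel test will be supplemented with a respective multivariate approach".

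**The concern.** Within each centre, exposure to PBM and calendar period coincide. A test stratified by centre alone therefore credits to PBM every change between the two periods: who is operated on, how care is delivered, and how diagnoses are coded. The last matters because the endpoint is taken from routine ICD-10 records. The staggered starts give some concurrent PBM and control hospitals, but the deciding test makes no use of them.

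The article recognises these threats and then handles them with a conditional step that cannot change the deciding test. With a margin of only 0.5 points, a small background fall could let a harmful programme pass, and a small rise could fail a safe one.

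**Working it through.** **Inputs.** From Sample size and power calculation: control rate 10%, margin 0.5 points, one-sided 2.5%, 80% power, about 100,000 patients. Not given, hence assumed: allocation ratio (1:1, with 1:2 as a check), size of drift (0.2-0.4 points; 0.4 is a 4% relative change in a 10% rate) and site start dates.

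**1. The plan's own figure.** "A power of 1 + β = 80% is sought". Per group, n = 2 × 0.10 × 0.90 × (1.960 + 0.842)² / 0.005² = 56,512, or 113,024 in total. With 100,000 at 1:1 the power is 75%. The article says that an exact calculation was not possible, so this is context and not part of the point.

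**2. Standard error of the centre-stratified difference.**
- 1:1: 100 × √(2 × 0.09 / 50,000) = 0.190 points.
- 1:2: 100 × √(0.09 × (1/33,333 + 1/66,667)) = 0.201 points.
- Illustrative staggered layouts (step 5): 0.20-0.22 points.

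At 0.19, non-inferiority is declared when the observed difference is below 0.5 − 1.96 × 0.19 = 0.13 points.

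**3. True harm equal to the margin, favourable drift D.** The observed contrast centres on 0.5 − D, so P(non-inferiority) = Φ(D/SE − 1.96).

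| D (points) | SE 0.19 | SE 0.22 |
|---|---|---|
| 0 | 2.5% | 2.5% |
| 0.2 | Φ(−0.91) = 18% | Φ(−1.05) = 15% |
| 0.3 | Φ(−0.38) = 35% | Φ(−0.60) = 28% |
| 0.4 | Φ(0.15) = 56% | Φ(−0.14) = 44% |

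A 1:2 allocation gives 16.6%, 31.8% and 51.0%. Working on the odds-ratio scale against OR* = (0.105/0.895)/(0.10/0.90) = 1.056 changes these by about 2 percentage points at most.

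**4. No true effect, unfavourable drift of 0.2 points (SE 0.19).** Power = Φ((0.5 − 0.2)/0.19 − 1.96) = Φ(−0.38) = 35%. Without drift it is Φ(0.5/0.19 − 1.96) = 75%.

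**5. Is significance a good gate for drift?** Assumed layouts: four equal centres, 24 or 30 months, starts staggered by 1 to 6 months, the three implementation months dropped, and a linear trend fitted with PBM and centre.
- The standard error of the trend is 0.22-0.33 points per year.
- The mean time between control and PBM patients within a centre is (24 + 3)/2 = 13.5 months or (30 + 3)/2 = 16.5 months.
- The standard error of the drift over that gap therefore runs from 0.219 × 1.375 = 0.30 to 0.333 × 1.125 = 0.37 points.
- A 0.4-point drift then reaches two-sided 5% significance in 19-26% of cases. In four of the five layouts the figure is 19-21%.

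**6. What time adjustment costs in these layouts.**
- Linear trend: SE 0.37-0.43 points, which is 1.7 to 2.1 times the centre-only value (0.374/0.220; 0.425/0.199).
- Quarter effects in layouts of 10-12 quarters: SE 0.40-0.55 points.
- Power at zero true difference: Φ(0.5/0.38 − 1.96) = 26% at SE 0.38, falling to Φ(0.5/0.55 − 1.96) = 15% at SE 0.55.
- The least favourable layout tried (30 months, two-month steps, quarter effects) has SE 0.69 points and power 11%.

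**The case against.** **The article does not ignore time.** Calendar year and site asynchrony are to be assessed whatever happens; only the adjustment is conditional. It would be wrong to say that the staggered start goes unused altogether. It goes unused in the deciding test.

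**The adjusted analysis may well be run.** The text can be read as having one trigger and one multivariate model. A comorbidity with an odds ratio of 1.2 and 20% prevalence (assumed) would give z of about 7 in 100,000 patients, so the trigger would fire, and calendar year might then be in the model. The 19-26% figure applies if each covariate is gated separately, which the article does not specify. Even on the generous reading, the adjusted result only supplements the deciding test.

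**Two stronger readings fail.** A reader might infer that pre-testing covariates breaks the 2.5% error rate. It does not: the gate never alters the Mantel-Haenszel test, and the inflation in step 3 comes from confounding by drift. A reader might also infer that nothing says which result decides. The natural meaning of supplementing a named primary test is that the named test still decides.

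**Adjusting for time is expensive.** This stands. Step 6 shows that forcing a calendar term into the deciding analysis could make even a safe programme likely to fail. Accrual ends in July 2015 and PBM is already in place at all four hospitals, so neither sample size nor stagger can readily be changed.

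**Conclusion.** The concern holds as a fault in a rule that the article fixes, not as a detail left to an analysis plan. The deciding comparison is non-randomised and before-after, and it is adjusted for centre alone. The only remedy offered is gated by significance and leaves the verdict untouched.

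Under assumed drifts of 0.2 to 0.4 points, all below the margin, the chance of wrongly declaring non-inferiority rises from 2.5% to somewhere between 15% and 56%. Drift in the other direction costs a neutral programme about half its power. These figures rest on 100,000 patients, a 10% rate, a standard error of 0.19-0.22 points and the normal approximation. The documents do not show that such drift occurred. They show that the deciding test has no protection if it did. The detection and precision figures in steps 5 and 6 depend on assumed start dates and are illustrative.

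**What to change.** 1. Delete the significance trigger.
2. Let one pre-specified logistic model decide non-inferiority. It contains PBM, centre and baseline case mix already held in the hospital system (for example age, surgical specialty, urgency, concomitant diseases). Standardise it to a risk difference and compare the upper confidence limit with 0.5 points.
3. Do not compare its conditional odds ratio with OR*. OR* comes from overall incidences, and odds ratios are non-collapsible. With an assumed case-mix standard deviation of 1.0-1.5 on the logit scale, 0.5 points corresponds to a conditional odds ratio of 1.062-1.069, so using 1.056 would tighten the margin to about 0.45-0.40 points.
4. Keep the centre-stratified Mantel-Haenszel test as supportive.
5. Always report, whatever its p-value, the same model with a calendar-time term whose form is fixed in advance and which uses the staggered starts. Treat it as a key sensitivity analysis, and temper the non-inferiority conclusion if it disagrees with the deciding model.

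**Cost.** Case-mix adjustment needs only a change of wording and data already recorded. It removes confounding by measured case mix but not drift in coding or care, which only the calendar-time analysis addresses. That analysis is imprecise: an interval roughly two to three times as wide, with power of about 15-26% at 100,000 patients in most layouts tried. The report should state this limit. Whether to make the time-adjusted model the deciding one is a trade-off between bias and precision for the sponsor; if it is chosen, the power must be restated.

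### Secondary endpoints are tested without centre stratification, so if a hospital's PBM share is related to its usual stay or transfusion level, hospital differences can mimic or hide a PBM effect

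*Protocol article*

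**What the plan says.** All references are to the protocol article; no separate SAP is shown.

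- **Secondary test** (Statistical analysis): "Secondary endpoints will be compared with a two-sided Wilcoxon-Mann–Whitney test", at the 5% level. No stratification or adjustment is attached. The endpoints, listed under Secondary endpoints, are ICU stay, hospital stay and use of blood products.
- **Primary test** (same section): the aim is "non-inferiority of the intervention (PBM) cohort when compared with the control cohort stratified by center", and for the composite, "It will be analysed with a one-sided Mantel-Haenszel test with significance level of α =2.5% for the odds ratio".
- **Covariates** (same section): calendar year, concomitant diseases and the asynchrony of site periods are to be assessed. The remedy depends on an influence on the composite endpoint's incidence, and it supplements only the Mantel-Haenszel test.
- **Design** (Trial design): "Different time slots for control, implementation and study phases according to a non-randomised stepped wedge trial design" were allocated.
- **End of the PBM period** (Participants): "Patients treated after implementation will be allocated to the PBM cohort until July 2015".
- **Centre differences**: Background notes that transfusion practice varies between hospitals. Sample size and power calculation says patient numbers differ across the four hospitals and expects about 100,000 patients in all.

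**The concern.** The ordinary Wilcoxon-Mann-Whitney test compares all PBM patients with all control patients, whichever hospital treated them. Suppose one hospital supplies a larger part of the PBM cohort than of the control cohort and also keeps patients longer or transfuses more. Its level then shifts the PBM distribution although PBM changed nothing. The shift can go either way, so a PBM effect can be created or concealed.

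The design makes unequal shares plausible. Start times are staggered and the PBM period ends at the same time everywhere, so a later start leaves a shorter PBM period. With about 100,000 patients, the rank test will flag very small shifts. The primary analysis guards against the between-hospital part of this by stratifying; the stated secondary analysis does not.

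**Working it through.** The article gives no figure for the secondary endpoints, so there is none to reproduce. The question is how the stated test behaves when PBM has no effect.

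**Inputs.** From the article: four centres, about 100,000 patients, two-sided 5%. Assumed, because the article is silent: 25,000 patients per centre; PBM shares 65/55/50/45%; log-normal stay with log-SD 0.8; centre geometric means of 6.1/6.0/5.9/5.8, 6.3/6.1/5.9/5.7 or 6.6/6.2/5.8/5.4 days (spans of 0.3, 0.6 and 1.2 days).

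**Cohorts.** PBM: 25,000 × (0.65 + 0.55 + 0.50 + 0.45) = 53,750. Control: 100,000 − 53,750 = 46,250. The centres make up 30.2/25.6/23.3/20.9% of the PBM cohort and 18.9/24.3/27.0/29.7% of the control cohort.

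**Formula.** Let μ be a centre's log geometric mean, and v and w its weights in the control and PBM cohorts. The probability that a random PBM stay exceeds a random control stay is

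p = Σᵢ Σⱼ vᵢ wⱼ Φ[(μⱼ − μᵢ) / (0.8√2)].

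Its standard error under the null is √[(N + 1) / (12 × 46,250 × 53,750)] = 0.00183. With d = (p − 0.5) / 0.00183, the rejection rate is Φ(−1.96 − d) + 1 − Φ(1.96 − d).

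**Example.** Smallest span, highest share paired with longest stay: p = 0.50193, d = 1.06, rejection rate 18.4%.

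**All 24 pairings of the four means with the four shares:**

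| Span of means | Minimum | Average | Maximum | Shares and stays in the same order | Largest spurious difference in weighted means |
|---|---|---|---|---|---|
| 0.3 days | 5.1% | 9.6% | 18.5% | 18.4% | 0.03 days (0.8 h, about 0.5%) |
| 0.6 days | 5.2% | 23.0% | 55.7% | 55.3% | 0.07 days (1.6 h, about 1%) |
| 1.2 days | 5.5% | 54.8% | 98.8% | 98.7% | 0.13 days (3.1 h, about 2%) |

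In each row, 12 pairings make PBM stays look longer and 12 make them look shorter.

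**Equal shares.** If every centre has the same PBM share, then v = w, p = 0.5 and the rate is 5.0% whatever the centre differences.

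**Other share patterns**, with shares and levels in the same order and a log-scale centre range of 0.05, 0.10 or 0.20:

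- control shares 35/38/42/45%: 8.6%, 20% and 60%;
- control shares 30/40/45/50%: 19%, 57% and 99%.

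**Stratified test.** The van Elteren test rejected in 3.7% of 1,500 simulated trials with control shares 30/40/45/50% and range 0.20. The unstratified test rejects about 99% of the time in that setting.

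**Blood use.** A zero-inflated red-cell count was simulated with the 65/55/50/45% shares, again in the same order. With transfusion rates of 17/16/15/14% the unstratified test rejected 30.5% of the time and the stratified test 7%. With 18/16/14/12% the figures were 81.5% and 5%. These rates are also assumptions.

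**The case against.** - **Bias is not established.** A reader might infer that centre confounds every secondary comparison and that hospital differences will be taken for PBM effects. The documents do not support that. Bias needs PBM shares that differ between centres and are associated with the centre's level. The article gives no per-centre dates, control-period lengths or counts. This stands, and the point is therefore conditional.
- **Volume alone does nothing.** A large hospital has the same PBM share as a small one if their periods match and throughput is steady. Unequal period lengths or changing throughput are needed. This stands.
- **The highest rates assume an unfavourable alignment.** Pairing the highest share with the longest stay gives close to the worst result. The 24-pairing range and average are the fairer summary.
- **Significance is not importance.** The spurious differences come to a few hours of stay at most. This stands for the assumed scenarios, but a bare p-value at 5% would not show it.
- **The secondary endpoints do not carry the effectiveness claim.** A reader might infer that they do. The article labels the composite its primary efficacy endpoint, and the abstract frames effectiveness in terms of clinical outcome. The Background remark on transfusion practice is general; it is not data on these four hospitals and does not address length of stay.
- **An SAP might stratify.** Possibly, and an article does leave detail to it. But the article names a specific test here and, in the same section, attaches centre stratification only to the primary comparison. That is a stated choice open to improvement, not missing detail.

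**Conclusion.** The concern holds in conditional form. The stated secondary test does not protect against between-hospital differences in a staggered, non-randomised design, and no stated remedy reaches these endpoints. Whether bias arises, in which direction and how large, cannot be determined from the article.

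Under the assumptions above, the false-positive rate at nominal 5% lies between about 5% and 18.5%, 56% or 99% for centre means spanning 0.3, 0.6 or 1.2 days, averaging 10%, 23% and 55% over the possible alignments. The spurious difference is at most about 0.5%, 1% or 2% of stay, and it is zero when shares are equal. The primary non-inferiority test is not affected. The change is worth making because it is nearly free and because a large sample makes small artefacts significant.

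**What to change.** Replace the secondary test with the van Elteren test (Wilcoxon stratified by centre), two-sided at 5%, for every secondary endpoint. Beside each test, report an effect estimate with a 95% confidence interval, such as the difference in mean days or mean red-cell units, from a model containing centre and calendar time.

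State those terms for the secondary endpoints directly. They should not be borrowed from the primary covariate model, which the article makes conditional and for which it lists covariates only as examples. Calendar time is needed because stratifying by centre leaves time trends within centres untouched.

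The cost is a sentence or two in the plan and slightly more analysis work. Centre is already needed for the primary analysis, and calendar year is among the covariates to be assessed, so no new data are required. If centres prove balanced, the stratified test loses little or no power. Adjusting for calendar time may widen the intervals, because time and PBM exposure overlap in this design; that width is a fair statement of what the data can show.

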### Management

For consistent implementation regular teaching sessions were held at the beginning of the program and are repeated every six months. The focus is on clinical practice, outcome and safety issues in order to increase knowledge on PBM and awareness of the clinical implications of anaemia and the need for alternatives to transfusion. The new program is additionally promoted through hand outs, posters, checklists and web-based information among health care providers and patients.

Our PBM program has three main pillars:**Preoperative optimisation of haemoglobin levels:**

The preoperative detection, evaluation and therapy of anaemia diagnosis and treatment focuses specifically on those patients (aged 18 years and older) scheduled for elective surgery. Figure 1 shows the work-flow used at the University Hospital Frankfurt. Surgeries associated with a risk for transfusion >10% were identified by retrospective analysis of hospital data from 2011 with the hospital-information system Agfa ORBIS. Patients scheduled for elective surgery falling in that spectrum are screened and treated at the earliest possibility according to NATA and SABM recommendations if surgery can be postponed for at least four days (Figure 1) [12]. Iron deficiency anaemia (IDA) is treated with intravenous iron. Anaemic patients are suggested to be scheduled for both haematological and/or gastroenterological consultations for further diagnostics and optimal treatment of anaemia in cases where iron deficiency anaemia is unlikely.

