**Algorithm for the detection, evaluation and management of anaemia at the University Hospital Frankfurt.**

b)**Standardisation of transfusion practice according to evidence-based guidelines:**

Lectures on transfusion triggers according to the Cross-Sectional Guidelines for Therapy with Blood Components and Plasma Derivatives of the German Medical Association [13]. The strict enforcement of guideline-based transfusion triggers for surgical patients is supported by checklists attached to each RBC and/or during electronic documentation of the indication for RBC in patient’s record (Figure 2) and during the perioperative process (Figure 3).

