### Secondary endpoints

Length of stay on the intensive care unitTotal hospital stayQuantitative utilisation of allogeneic RBC units, platelet concentrates, other blood products

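### Blood products: the endpoint is the quantity used, but the only test named for it responds mainly to whether a patient was transfused at all (minor)

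*Protocol article*

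**What the plan says.** The Secondary endpoints section of the protocol article lists ICU stay, total hospital stay and quantitative "utilisation of allogeneic RBC units, platelet concentrates, other blood products". For blood products the outcome is therefore an amount, not a yes/no.

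The Statistical analysis section gives one rule for all of these: "Secondary endpoints will be compared with a two-sided Wilcoxon-Mann–Whitney test", at a 5% level. It names no other analysis of blood use.

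Three further statements matter:
- Participants: "The PBM program includes all patients undergoing surgical procedures", with exclusions only for age under 18 and for ophthalmologic, dermatologic and outpatient surgery.
- Management: "Surgeries associated with a risk for transfusion >10% were identified by retrospective analysis of hospital data", in order to choose which elective patients are screened for anaemia.
- Management, part b: adherence to transfusion triggers is "supported by checklists attached to each RBC" and by electronic documentation of the indication.

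The overall share of patients transfused is not given.

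**The concern.** A rank test compares whole distributions. When a large block of patients is tied at zero, nearly all of the rank information lies in who is above zero. How many units the transfused patients received adds very little.

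The population includes specialties with little transfusion, and the article uses a transfusion risk above 10% to single out certain operations. A majority at zero is therefore a reasonable guess for red cells, and more so for platelets and other products.

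The trigger checklist goes with each red cell unit, so one plausible effect of the programme is fewer units per transfused patient. The planned test hardly sees that effect. A real saving could be reported as no difference in blood use, although the Background and Discussion both give sparing a scarce resource as a motive for such programmes.

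**Working it through.** The plan states no figure for the secondary endpoints, so there is none to reproduce.

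**Inputs from the article.** Two-sided test at 5%; total size from Sample size and power calculation: "we expect approximately 100,000 participating patients".

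**Assumptions not in the article.** Equal cohorts, 100,000 / 2 = 50,000 each; share transfused p from 10% to 20%, with 30% as a further case; 4.0 units per transfused patient in the control cohort. Units among the transfused are 1 plus a negative binomial count with size 0.5 or 1 (right-skewed).

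**Step 1: how the rank statistic splits.** Let θ = P(PBM > control) + ½ P(tie), p0 and p1 the shares transfused in the control and PBM cohorts, and θu the same quantity among transfused patients only. Then

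θ − 0.5 = ½(p1 − p0) + p0·p1·(θu − 0.5).

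A change in units among the transfused is multiplied by p0·p1. At 15% in both cohorts that is 0.15² = 0.0225.

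**Step 2: one case in full.** p = 15% in both cohorts, units per transfused patient 4.0 → 3.6, size 1.
- θu = 0.4697, so θ − 0.5 = 0.0225 × (−0.0303) = −0.00068.
- Tie-corrected SE = √[(1 − Σ pooled³)(N + 1)/(12mn)], where the sum runs over the pooled proportions at each number of units. The zero block dominates it: 1 − 0.85³ ≈ 0.386. So SE ≈ √[0.386 × 100,001/(12 × 50,000²)] = 0.00113.
- z = −0.00068/0.00113 = −0.60; two-sided power about 9%.
- Means: 0.15 × 4.0 = 0.600 and 0.15 × 3.6 = 0.540 units per patient. The variances are 3.84 and 3.06, so SE = √[(3.84 + 3.06)/50,000] = 0.0117. Then z = −0.060/0.0117 = −5.1; power above 99%.
- Units saved in the PBM cohort: 50,000 × 0.060 = 3,000.

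**Step 3: the range** (10% fall in units per transfused patient, share unchanged; the two ends are size 0.5 and size 1).

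| Share transfused | Units saved | Rank-test power | Power for means |
|---|---|---|---|
| 10% | 2,000 | 5.5–6.2% | 94.5–98% |
| 15% | 3,000 | 7–9% | 99–100% |
| 20% | 4,000 | 10–16% | 100% |
| 30% | 6,000 | 24–45% | 100% |

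For a 20% fall (size 1), rank-test power is 10.4%, 24.9%, 52.5% and 97.5% at 10%, 15%, 20% and 30% transfused. The weakness fades as fewer patients are at zero.

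**Step 4: how near to a yes/no test.** Under the size 1 model, any use against none accounts for 99.6% of the variance of the ranks at 10% transfused, 98.4% at 20% and 96.0% at 30%.

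**Step 5: the opposite mechanism.** Units per transfused patient stay at 4.0 and the share falls by 7% of its value (for example 15% → 13.95%). Over 10–20% transfused, rank-test power is 96–100% and power for means is 67–98%. If instead the 1.05% of patients who avoid transfusion would each have had a single unit, the rank test gives z about −4.2 and the means z about −0.8 (power 11–14%).

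**The case against.** The strongest reply is that the rank test suits the programme's aim. The Background speaks of minimising unnecessary exposure to transfusion, and step 5 shows that the planned test is the more powerful one for avoided exposure. This stands: neither analysis dominates, and replacing the rank test would be wrong. When share and units per user both fall (7% and 10%), both analyses are significant.

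Second, the share at zero is an assumption. This also stands. The 10% threshold only selects operations for anaemia screening and supports the assumption indirectly.

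Third, an unseen analysis plan may add summaries, and Economic evaluation already compares average cost per group with blood products as an input. That is fair, but cost is not units, and the article itself fixes a rank test for an endpoint it defines as a quantity.

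Two stronger readings are tempting and are not supported:
- *The test may declare a reduction while total units rise.* In this model that needs the share to fall while units per transfused patient rise. With 15% → 13.95% and 4.0 → 4.6, total units go from 0.600 to 0.642 per patient (+7%; means z = +2.7 to +3.2), while the rank test gives z = −4.0 to −4.2. Sparing single-unit patients cannot produce this: the mean among users would rise only to (0.600 − 0.0105)/0.1395 = 4.23, and total units would fall. Nothing in the article suggests heavier transfusion of the remaining patients.
- *ICU stay has the same defect.* The article does not say whether patients without an ICU stay count as zero. If only ICU patients are compared, the argument disappears.

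**Conclusion.** The point holds for blood products only, as a minor one. The test is valid for a difference in distribution; the fault is its mismatch with an endpoint defined as a quantity. A non-significant rank test could not be read as no change in units used: with 10–20% transfused, a 10% saving per transfused patient would be missed in roughly 84–94% of trials, although a comparison of means would nearly always show it.

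This rests on the assumed share transfused, 4 units per transfused patient, equal cohorts and a right-skewed count. It weakens as the share transfused rises, and it does not apply if the programme acts mainly by avoiding transfusion. The primary non-inferiority conclusion is unaffected.

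**What to change.** Keep the Wilcoxon-Mann-Whitney test. In the Statistical analysis section, add for blood products the centre-stratified difference in mean units per patient, expressed per 1,000 patients, with a robust-variance or bootstrap 95% confidence interval. Show beside it the proportion transfused and the mean units among those transfused. State that any conclusion about the quantity of blood used rests on this estimate and not on the rank-test p-value.

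The cost is a few lines of wording and slightly more analysis, on data the trial already collects. The mean is sensitive to massive transfusion and has less power for avoided small transfusions, which is why the proportion transfused must stand next to it.
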